## Abstract

**Background:**

Antenatal care (ANC), facility delivery and postnatal care (PNC) are proven to reduce maternal and child mortality and morbidity in high-burden settings. However, few pregnant rural women use these services sufficiently. This study aims to assess the impact, cost-effectiveness and scalability of conditional cash transfers to promote increased contact between pregnant women or women who have recently given birth and the formal healthcare system in Kenya.

**Methods:**

The intervention tested is a conditional cash transfer to women for ANC health visits, a facility birth and PNC visits until their newborn baby reaches 1 year of age. The study is a cluster randomized controlled trial in Siaya County, Kenya. The trial clusters are 48 randomly selected public primary health facilities, 24 of which are in the intervention arm of the study and 24 in the control arm. The unit of randomization is the health facility. A target sample of 7200 study participants comprises pregnant women identified and recruited at their first ANC visit over a 12-month recruitment period and their subsequent newborns. All pregnant women attending one of the selected trial facilities for their first ANC visit during the recruitment period are eligible for the trial and invited to participate. Enrolled mothers are followed up at all health visits during their pregnancy, at facility delivery and for a number of visits after delivery. They are also contacted at three additional time points after enrolling in the study: 5–10days after enrolment, 6 months after the expected delivery date and 12 27 months after birth. If they have not delivered in a facility, there is an additional follow-up 2 wees after the expected due date. The impact of the conditional cash transfers on maternal healthcare services and utilization will be measured by the trial’s primary outcomes: the proportion of all eligible ANC visits made during pregnancy, delivery at a health facility, the proportion of all eligible PNC visits attended, the proportion of referrals attended during the pregnancy and the postnatal period, and the proportion of eligible child immunization appointments attended. Secondary outcomes include; health screening and infection control, live birth, maternal and child survival 48 h after delivery, exclusive breastfeeding, post-partum contraceptive use and maternal and newborn morbidity. Data sources for the measurement of outcomes include routine health records, an electronic card-reader system and telephone surveys and focus group discussions. A full economic evaluation will be conducted to assess the cost of delivery and cost effectiveness of the intervention and the benefit incidence and equity impact of trial activities and outcomes.

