### Intervention strategy

#### Cash transfer value

The intervention is a conditional cash transfer (CCT) payment for each facility appointment attended for ANC, delivery, postnatal care and childhood immunization; and referrals related to any of these visits. For each verified health visit that is made on time following enrolment, a woman receives a cash transfer of Ksh 450 (4.5 USD). The value reduces by one quarter for each week of delayed visit, and no reward is offered for any visit made 3 weeks after the appointment date. On average, Ksh 450 equates to the transportation cost of a local taxi to the health facility, and is a value that has been approved by the research ethics committee for many studies in the region as reasonable compensation for research participants.

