**Fig. 2 Fig2:**
[figure not shown]
Theory of change. MNCH, maternal, newborn and child health; ANC, antenatal care; PNC, postnatal care; EBF, Exclusively breastfeeding

The rationale for the use of a CCT intervention is found in behavioural economic theory, which suggests that individuals commonly have inconsistent preferences for similar outcomes occurring at different points in the future, with outcomes in the near future generally valued more than those in the distant future [31, 32]. According to Giles et al. [33], while the health gains of health-promoting behaviours are often delayed in time, the financial and opportunity costs are usually immediate. Individuals thus make a rational choice to pursue unhealthy behaviours or delay spending on health-promoting activities in the present but with future benefits. Cash transfers work by bringing long-term goals into the short-term decision horizon by providing immediate rewards and reducing current costs [33].

This study is based on the theory that cash transfers overcome direct and indirect financial and behavioural barriers to healthcare attendance during pregnancy, delivery and the postnatal period, and in so doing would lead to more regular use of services compared to current practice. Retention of women in the care continuum from pregnancy through the postnatal period will have a positive impact for MNCH interventions that require regular treatment and follow up.

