#### Collecting data on visits to facilities outside the study area

The strategies used to collect these data vary according to whether or not the participant is considered high risk. High-risk groups in this study comprise mothers whose ANC records show HIV-positive status, positive malaria smear test and/or other diagnoses of sexually transmitted infection (STI). These diagnoses are likely to require referrals and additional health visits not captured in routine ANC or PNC records. Furthermore, participants with these complications are more likely to be lost to the routine monitoring systems as they might completely shift their ANC, delivery and PNC visits to the referral centers that handle these infections.

We will track all health visits made by high-risk participants only, including those taking place in neighbouring counties outside the evaluation zone. This would be done through extra phone calls to the participants to elicit information on health facilities visited. The study team will then visit those facilities and manually extract health records as described previously. The exception to this case would be if care is sought outside the Western Kenya region, in which case the data will be considered missing in the case of a single instance of care seeking, or the participant will be classed as lost to follow up if they have permanently transferred.

For lower risk participants, we shall incorporate questions relating to the primary outcomes (facility visits, child vaccinations etc.) into the telephone surveys (see Telephone surveys) administered to 50% of participants. This gives participants the opportunity to report visits both outside the study area and within, and we shall also ask whether the participant moved temporarily or permanently outside the study area. By comparing these self-reports with the data on visits within the study area (collected by other means) we will be able to approximately deduce the number of visits made outside the study area. These additional visits will not be verified by the study team as will be done for high-risk participants.

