It is also expected that the intervention will increase demand for health services. However, no expansion in health service supply is planned and as such, the increase in demand will likely increase the workload of existing staff. To capture any unanticipated impact on effort, data on health workers’ motivation and satisfaction [35] will be collected in both arms of the trial. A less motivated health worker may perform adequately in minimally demanding conditions, but their willingness to exert extra effort might depend on whether they feel there is personal value in doing so [36]. Further, if a workplace is not conducive to effective working, or if health workers do not have the knowledge, skills or experience to complete their tasks, they might be demotivated. Thus, health worker motivation is the ability and willingness to put in the effort required to do the job, influenced by individual factors (such as knowledge, skills, experiences, psychological attributes) and organisational factors (such as physical and social environment, policies and practices) [37]. Organisational factors are more likely to change than individual personality tendencies, or societal and cultural values. Thus, with the introduction of the card system and the potential increase in the demand for MNCH services, health worker motivation is likely to be affected, with consequences for service delivery. A self-completion motivation and job satisfaction survey will thus be administered to all participating health staff. Collecting and analysing these data will allow us to explore how the intervention could affect health worker motivation and satisfaction [38], and potentially service delivery.

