#### Final analysis

Final analyses will be by intention-to-treat, based on all enrolled mothers who were pregnant during the recruitment period (July 2017 to July 2018) and their children, regardless of whether they received the intervention or not. We will test for differences in the primary outcomes between the intervention and control arms using logistic regression for binary outcomes, and ordinal logistic regression for ordinal outcomes, adjusting for clustering using random effect models.

Provided there is no qualitative difference between the odds ratios for the effect of the intervention across the primary outcomes, then only the summary odds ratio will also be presented. This will be the primary effect measure for the trial. It will be estimated using independence estimating equations because not all participants will be eligible for all outcomes (e.g. vaccination of infants who died) and this approach avoids any implicit imputation of outcomes for ineligible participants.

Besides the issue of ineligible outcomes described previously, there should be no completely missing data on the primary outcomes. If a record of attendance cannot be found in the patient records in the study area, this will be interpreted as failure to attend. However, participants may make visits to facilities outside the study area, often in relation to temporarily or permanently moving to reside outside the study area. As described in Section Collecting data on visits to facilities outside the study area, data on visits outside the study area will be available for all higher-risk participants, and dependent on telephone interviews also available (though approximate) for up to half the lower-risk participants.

We plan to conduct our primary analysis based only on data on lower-risk participants from visits within the study area if it seems this will not lead to bias, but to use the approximate number of visits outside the study area from (up to) half the lower-risk participants to impute these additional visit data for the remaining participants if it seems bias will otherwise arise. We prefer not to impute visits out of the study area unless this is required because the data on visits outside the area by lower-risk participants are only approximate.

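### The referral outcome is a proportion of referrals issued, and the cash can change which referrals are issued, so this primary comparison is not fully protected by randomisation

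*Protocol article*

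**What the plan says.** The Abstract lists "the proportion of referrals attended during the pregnancy and the postnatal period" among the primary outcomes. The Primary outcomes list and Table 1 repeat it as attended referrals over referrals for ANC, PNC and child immunization. The ANC, PNC and immunization outcomes in the same list are instead counted against appointments that are due, and delivery is counted against participants.

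On where referrals come from, Cash transfer value says payment covers ANC, delivery, "postnatal care and childhood immunization; and referrals related to any of these visits". The section on visits outside the study area says of HIV, malaria and STI findings in the ANC record: "These diagnoses are likely to require referrals and additional health visits not captured in routine ANC or PNC records".

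On what the cash is expected to do, the Theory of change says it "would lead to more regular use of services compared to current practice", and Process evaluation says it is "expected that the intervention will increase demand for health services".

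Final analysis describes intention-to-treat on all enrolled mothers. It chooses independence estimating equations for the summary odds ratio "because not all participants will be eligible for all outcomes (e.g. vaccination of infants who died"), so that nothing is imputed for women who cannot have the outcome. That summary is the trial's primary effect measure. It is presented provided the outcome-specific odds ratios do not differ qualitatively.

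**The concern.** A woman enters the referral denominator only once she has been referred. If referrals are mostly made at visits, and the cash produces more visits, the intervention arm will contain referrals that would not have been issued under control. The women behind those extra referrals may be less engaged with care and less likely to keep a referral. The arms would then be compared on differently selected women, even though the facilities were randomised.

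Final analysis treats eligibility as a question of missing outcomes and gives infant death as its example. It does not recognise that becoming eligible for this outcome may itself depend on the arm. Leaving out women with no referral is reasonable as a way to avoid imputation, but it does not make the remaining women comparable.

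At stake is the reading of one of five primary outcomes. A real effect on referral uptake could be masked, or an apparent effect could reflect selection. The outcome also feeds the summary odds ratio and the judgement on whether the five odds ratios agree well enough for that summary to be presented.

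**Working it through.** **The plan's own figures.** The plan states nothing about referral rates. Its sample size figures reproduce: 1 + 149 × 0.005 = 1.745 and 3600/1.745 = 2063; 1 + 149 × 0.025 = 4.725 and 3600/4.725 = 762. The point does not depend on them.

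**Two-group illustration (all inputs assumed).** Half the women are engaged and half less engaged. There are three visits after enrolment, and referrals are proportional to visits attended. Control attendance is 70% and 30% in the two groups; cash-arm attendance is 75% and 50%. Uptake once referred is 80% and 40% in *both* arms, so the cash has no effect on uptake.

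Proportion attended = Σ(weight × uptake)/Σ(weight), with weight = 0.5 × 3 × attendance.

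- Control: (1.05 × 0.80 + 0.45 × 0.40)/1.50 = 68.0%.
- Cash: (1.125 × 0.80 + 0.75 × 0.40)/1.875 = 64.0%.
- Difference −4.0 points; odds ratio (0.64/0.36)/(0.68/0.32) = 0.84; 1.875/1.50 = 1.25, so 25% more referrals in the cash arm.

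Variations:

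| Change to the assumptions | Difference (points) | Odds ratio |
|---|---|---|
| Enrolment visit also generates referrals | −2.2 | 0.91 |
| Smaller attendance gain (72%/40%) | −2.3 | 0.90 |
| Smaller uptake gap (70%/50%) | −2.0 | 0.92 |
| Smaller gain, smaller gap, with enrolment referrals | −0.6 | 0.97 |
| Same uptake in both groups (60%/60%) | 0 | 1.00 |
| Attendance unchanged by cash | 0 | 1.00 |

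Conversely, a true gain of 5 points in both groups would appear as +1.0 point, or +2.8 with enrolment referrals.

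**Simulation (all inputs assumed; 2 million women per arm).** There are eight scheduled visits. Attendance probability is expit(0.45 + log visit odds ratio + u), with u normal, SD 1.5. Each attended visit carries a 6% chance of referral. Uptake is expit(0.6 + b·u), with no cash effect. The outcome is that all referrals were attended, the binary form used in the Sample size section.

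| Attendance, control to cash | b = 0.5 | b = 1.0 |
|---|---|---|
| 58% to 66% | 67.0% to 65.4%, OR 0.93 | 69.5% to 67.1%, OR 0.90 |
| 58% to 73% | 67.0% to 64.1%, OR 0.88 | 69.5% to 65.1%, OR 0.82 |

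Adding one enrolment visit at the same 6% rate reduces the first row to −1.2 to −1.8 points (OR 0.95 to 0.92). If that visit refers three times as often, it is about −1 point (OR 0.96 to 0.95). With b = 0, the all-attended odds ratio is 0.97 to 0.98, only because more referrals per woman make it harder to attend all of them.

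**Effect on the summary odds ratio.** In this model 24% to 30% of women have any referral. Suppose the other four outcomes cover everyone at about 60% prevalence. The referral outcome's share of the information is then f·p(1−p)/[f·p(1−p) + 4 × 0.24], where f is the share of women referred and p the proportion attending all referrals. In the largest case f = 0.27 and p = 0.67, giving 0.059/(0.059 + 0.96) = 5.8%. The summary is multiplied by 0.82^0.058 = 0.989. In the smallest case of the table the multiplier is 0.996.

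**The case against.** No referral rate or uptake gradient is in the documents, so every figure above is an assumption. That referrals arise from attended visits is an inference. Study setting mentions referral from community level, and the section on outside visits ties referral need to diagnoses without saying when they are made. Referrals from the enrolment visit escape the attendance effect and dilute it. The PNC and immunization denominators also depend on events after allocation (live birth, infant survival), so the contrast with the other outcomes is one of degree. The clause on qualitative disagreement is a safeguard in itself. Referral visits are paid for ("and referrals related to any of these visits"), so their uptake is a legitimate target. All of this stands, and it limits the size of the point. None of it makes the referral denominator independent of the arm.

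Three stronger readings are tempting, and the documents do not support them:

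- *Cash-arm staff issue extra, less urgent referrals.* This would give a much larger bias: about −13 to −14 points if such referrals are assumed at 3% of visits with low uptake, or a bias of the opposite sign if they are easy to keep. Staff are paid per woman enrolled, not per referral, and no such behaviour is described.
- *The analysis is not intention-to-treat.* Final analysis includes all enrolled mothers whether or not they received the intervention, and it says openly that not all are eligible for every outcome. Only the referral contrast is conditional in the sense described here.
- *The primary effect measure is badly distorted.* In the visit-driven case the shift is about 1% or less.

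**Conclusion.** The point holds as a structural weakness of one primary outcome. On the protocol's own account, the cash is expected to raise the visits from which referrals appear to arise, and the planned estimating equations do not restore comparability. Bias requires both that attendance changes and that uptake differs between the added referrals and the rest; if either fails, it is about nil. Within the assumptions shown, and with no true effect on uptake, the odds ratio runs from about 0.82 (large attendance gain, steep gradient, no enrolment referrals) to 0.97 (small gain, shallow gradient, enrolment referrals included). These are illustrations. The documents establish neither size nor direction. The effect on the summary odds ratio is probably small, because referral covers a minority of women in the model used. The change is worth making because it is cheap and concerns a primary comparison.

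**What to change.** In Final analysis:

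1. State that the referral comparison is conditional on a post-randomisation event, namely being referred.
2. Report by arm the number of women referred, and the referrals issued and attended per enrolled woman. These use all enrolled women as the denominator.
3. Add an analysis restricted to referrals issued at the enrolment visit, which every participant attended before any payment. It is less affected rather than immune, since facilities were allocated before women enrolled.
4. Present the summary odds ratio also without the referral outcome, and do not let the referral odds ratio alone decide whether the outcomes disagree qualitatively.

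Moving referral attendance to the secondary outcomes is open to the sponsor but not required. Trial status shows recruitment already closed, so that would be a late change to the primary outcomes and would need to be declared. The cost of the four steps is some wording and a little more analysis, with no new data. The enrolment-visit version will have fewer events and so less precision.

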**Discussion:**

This trial will contribute to evidence on the effectiveness and cost-effectiveness of conditional cash transfers in facilitating health visits and promoting maternal and child health in rural Kenya and in other comparable contexts.

**Trial registration:**

ClinicalTrials.gov, NCT03021070. Registered on 13 January 2017.

**Electronic supplementary material:**

The online version of this article (10.1186/s13063-019-3224-8) contains supplementary material, which is available to authorized users.

## Background

A “Continuum of Care” for reproductive, maternal, newborn and child health (RMNCH) includes integrated service delivery for mothers and children from pre-pregnancy to delivery, the immediate postnatal period and early childhood [1]. Assuring continuity of care has become a key programme strategy for improving the health of mothers and newborns, and is an important measure of service quality for outcomes such as prevention of mother-to-child transmission of HIV (PMTCT) [2]. Yet, in many countries, there remain major gaps in seeking care along this continuum. Retaining women in this continuum even during pregnancy has not yet been achieved in sub-Saharan Africa (SSA), with only 44% of women attending the minimum of four recommended visits that constitute focused antenatal care (ANC) [3]. Focused ANC is a scheduled service, and when clients do not adhere to the recommended timing or frequency, the effectiveness of the service is compromised. A number of complementary treatments provided during ANC have to be delivered in sequence for them to be effective. Examples include iron and folic acid supplementation, tetanus toxoid immunization, syphilis testing and treatment, counselling on maternal and infant nutrition and intermittent preventive treatment of malaria in pregnancy (IPTp) [4]. Postnatal services are equally essential, as half of all postnatal maternal deaths occur during the first week after delivery, and one in four child deaths occur in the first month of life [5]. In SSA, postnatal care programmes are among the weakest of all reproductive and child health programmes [6]. Follow-up treatment and services such as PMTCT, family planning, breastfeeding and infant feeding support and childhood immunization cannot be achieved if women are lost to care immediately after delivery, as is the current trend.

Complex structural, financial, cultural and behavioural factors contribute to gaps in care seeking in SSA [7, 8]. In Kenya, where maternal mortality rates are 488 per 100,000 live births, a lack of transport has been cited as one of the major contributing factors to low utilization of healthcare services [9]. In a national survey [9], the largest proportion of respondents (42%) reported that delivering outside a health facility took place because the facility was far away or they lacked transport to the facility. In comparison, only 17% cited the fees levied at the facilities as the key barrier [9]. Other barriers include the indirect costs of care seeking such as food for mothers and accompanying children, new clothes appropriate to be seen at ANC visits, and the opportunity cost of time away from farming or other income-generating activities [10]. Cultural barriers have also been reported. In Zimbabwe, Chapman [11] found that because women have high maternal morbidity and miscarriages in their communities, and at the same time are under high social pressure to bear children, they hide their pregnancies to protect themselves and the unborn child from witchcraft and sorcery. Lack of knowledge about the benefits of care seeking is yet another important barrier [10]. One study in Kenya showed that the motivation to attend ANC was driven by authority-linked factors, such as obtaining an ANC card to avoid reprimand or reduced care by the staff during birth [10]. The visits are therefore made late in pregnancy, and discontinued once the ANC card is obtained. In the light of these multiple challenges, an intervention targeted at only one of the barriers (e.g. removal of user fees, or provision of transport vouchers) will only have a limited impact.

Personal financial incentives (PFIs) may offer the broad-based solution needed to tackle low levels of care seeking and retention of women in the care continuum. PFIs can tackle both the financial barriers to care seeking and the motivational barriers. Several studies [12–15] have demonstrated how personal financial incentives (PFIs) can help to increase adherence to lengthy treatment schedules. In developed countries, paying people to change their behaviour has been effective in reducing excess consumption of high-fat foods, cigarettes, alcohol and illicit drugs [16]. Notable successes in developing countries include tuberculosis (TB) treatment programmes, where financial and material incentives directed to patients increased successful completion of TB treatment regimens [17, 18]. Outside the context of TB, PFI schemes in SSA remain largely untested. In the context of reproductive, maternal, neonatal and child health, few cash transfer programmes have been piloted, and none have targeted adherence to a scheduled programme or treatment schedule; instead the focus has been on a specific aspect of the care system such as ANC attendance or facility delivery [19, 20].

There is an opportunity to test the effectiveness of PFI as a broad-based intervention to improve maternal care-seeking behavior in the Kenyan context. Over two thirds of women come into contact with the formal healthcare system at least once during pregnancy [3]. A strategy that can retain these women in care, from their first contact in pregnancy through to delivery and the childhood period, could significantly alter the negative trends in maternal and child health in this context and possibly also in Africa more generally.

This trial is testing the effectiveness and cost-effectiveness of cash incentives in retaining women in the continuum of care from their first ANC visit until their children reach 1 year of age. It will be the first trial in SSA targeted at retaining women in the maternal, newborn and child health (MNCH) care continuum, and will generate crucial evidence to inform policy and practice. A secondary aim of the project is to assess the benefits of improved care-seeking in maternal and child health, and the cost-effectiveness of the intervention.

